##### Birth biologicals

These analyses will be guided by our models of the MPF axis, the first involving a cascade of effects via maternal cortisol to the child’s HPA axis functioning (diurnal and reactive cortisol), and second involving a cascade through the catecholamine/inflammatory system. We will begin by testing bivariate associations throughout the model, culminating in structural equation modelling, including testing of moderation of effects by fetal sex and by timing in gestation of the floods.

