**Model 1:***MPF neuroendocrine systems*. We propose that objective and subjective PNMS will activate a cascade of events leading to an increase in maternal, placental, and fetal cortisol terminating in altered HPA axis function and a lower stress response in the child. We predict that more severe objective/subjective PNMS will decrease activity of the placental/activity of the placental 11β-HSD2, resulting in increased levels of cortisol in placenta and fetal blood (cord blood). Moreover, more severe objective/subjective PNMS will also be associated with increased placental Corticotropin-releasing hormone (CRH) production that will, in turn, over-stimulate the maternal HPA axis and thus exacerbate maternal cortisol production and the inhibition of placental 11β-HSD2, resulting in higher levels of cortisol in placenta and fetal blood (cord blood).

**Model 2:***MPF immune systems and metabolic outcome*. We propose that more severe objective/subjective PNMS will be associated with increased maternal catecholamine levels (physiological response to stress) resulting in an abnormally high level of oxidative stress and pro-inflammatory cytokines in the placenta that will increase inflammatory and oxidative status of maternal and fetal blood, which will cause an increase risk in obstetric complications (such as preterm birth, low birth weight, intrauterine growth restriction and preeclampsia), which may then go on to predict future risk for metabolic and psychiatric difficulties in children later in life.

**Model 3:***Birth weight and body composition*: We propose that higher placental cortisol levels will cause a decrease in the production of placental hormones regulated by glucocorticoids (such as human placental lactogen (hPL), placental growth hormone (pGH), leptin, estrogens, progesterone, and glucose transporter type 1(GLUT1; lower maternal-fetal glucose exchange)) resulting in a lower placental efficiency (lower birth weight and higher placental weight), resulting in fetal growth restriction and/or altered programming of body composition in the child. We hypothesize also that maternal and fetal glucose, insulin, leptin, and other adipocytokines in blood will be involved in this process.

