## Methods/design: QF2011

### Participants

All women who agreed to participate in the study provided written informed consent. Inclusion and exclusion criteria differed slightly for M@NGO [63, 64] and for QF2011. Women were eligible for recruitment to the M@NGO trial if they were less than 24 weeks pregnant and were not planning caesarean section birth; QF2011 participants had to have been pregnant with a singleton pregnancy (at any gestation) and residing in the general vicinity of Brisbane on January 10, 2011. All participants were 18 years of age or older at recruitment, and were able to speak English fluently.

Recruitment for QF2011 began as soon as ethics approval was received (April 4, 2011), and continued to mid-January 2012 (12 months after the peak of the flood); as per original protocol, recruitment for M@NGO ceased on May 31, 2011 in both Sydney and Brisbane. Recruitment proceeded in 4 ways:When new participants were recruited into M@NGO, they were also presented with the QF2011 protocol, and invited to participate in either or both studies. M@NGO recruitment at the Mater Hospital involved face-to-face, phone, and e-mail recruiting following a routine mail-out describing the study to all women attending the antenatal clinic.The team contacted all existing M@NGO subjects who were eligible for QF2011 first by e-mail, then by cell phone (text message), then by telephone inviting them to also participate in the new flood study.The team invited women who were pregnant and eligible for the QF2011 study, but not eligible for M@NGO, or who would have been eligible for M@NGO but were approached after M@NGO recruitment ceased, to participate in QF2011. A flyer inviting women to participate and to contact the recruitment team was included in the routine mail-out from the antenatal clinic. A researcher in the antenatal clinic actively recruited participants face-to-face on site and was available to speak to midwives and other potential participants about the study.Finally, advertisements were placed in local newspapers, on radio, and on the internet for women who were pregnant at the time of the floods (even if they had already delivered).

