#### Biological samples: mother, birth, and child

##### Maternal pregnancy blood samples (36 weeks gestation)

Women still pregnant at the time of recruitment had additional blood drawn for the purposes of QF2011 at the time of routine antenatal blood tests collected at 36 weeks gestation. An additional 4 × 5ml vials were drawn, centrifuged, then stored at -80°C (plasma and serum). Blood samples will be analyzed for (a) endocrine markers; (b) immune panel (cytokines); and (c) biomarkers of nutrition panel.

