## Discussion

Two 2011 *Nature* papers show that the production of greenhouse gases is responsible for the ever increasing risk of flooding [156, 157]. Prenatal stress research suggests that severe weather events increase the risk for adverse effects in the offspring, via fetal programming, that convey a huge public health burden. The goal of designing interventions for pregnant women in disasters or other stressful situations, to circumvent the effects of stress on the fetus, requires better understanding of the MPF mechanisms involved. The QF2011 study will increase current knowledge about the cascade of effects from an external event to the mother, through placenta and cord, to a host of outcomes in the unborn child. The pre-flood psychological assessments, biological samples at birth, and the embedded midwifery RCT examining the effect of Midwifery Group Practice, have provided a unique opportunity to compile the most comprehensive prospective data set ever obtained to study the effects of an independent stressor on child-bearing women, and risks for PTSD, postpartum depression, pregnancy outcomes, and infant development. By obtaining a multitude of maternal, placental and infant biomarkers from a large sample of women exposed to the flood at different points during pregnancy, we can bring the entire human maternal-placental-fetal system into the laboratory, and test integrated biopsychosocial models of prenatal stress for the first time. Armed with a better understanding of the processes involved, intervention strategies to prevent adverse outcomes in both mother and child can be designed and tested.

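### Birth-sample and 36-week-blood models have no data for late-pregnancy flood exposure, and 36-week blood cannot inform births before 36 weeks

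*Protocol article*

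**What the plan says.** **Eligibility and dates (Participants).** "QF2011 participants had to have been pregnant with a singleton pregnancy (at any gestation"). The reference day is 10 January 2011, and women had to live in or near Brisbane. On dates, the section says: "Recruitment for QF2011 began as soon as ethics approval was received (April 4, 2011), and continued to mid-January 2012". Women who had already delivered could still join.

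**Maternal blood (Maternal pregnancy blood samples).** "Women still pregnant at the time of recruitment had additional blood drawn for the purposes of QF2011", at the routine 36-week blood test.

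**Birth samples (Placenta; Umbilical cord; Cord blood; Table 1).** These were taken at or just after delivery. Table 1 marks them as QF2011 items, and the introduction to the QF2011 instruments describes the birth procedures as additions to the M@NGO protocol. M@NGO therefore could not have supplied them before QF2011 was approved.

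**Model 2 (Problem statement, objectives, hypotheses and research questions).** Stress in the placenta is said to leave the mother's and the fetus's blood more inflamed and oxidised, a change "which will cause an increase risk in obstetric complications (such as preterm birth, low birth weight, intrauterine growth restriction and preeclampsia").

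**Analysis (Birth biologicals).** Bivariate associations lead up to structural equation models, "including testing of moderation of effects by fetal sex and by timing in gestation of the floods". No exposure range is given.

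**Discussion.** The biomarkers are described as coming "from a large sample of women exposed to the flood at different points during pregnancy".

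**The concern.** Timing of exposure is one of the article's central moderators (Effect moderators), and the section on Project Ice Storm reports a late-pregnancy effect on motor outcomes. The biomarker models are meant to explain such effects. If the sampling dates leave late exposure empty, a timing-moderation result describes early and mid-pregnancy only, and nothing in the plan tells the reader so.

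Two selection problems follow from the same dates. A woman gives a birth sample only if she is still pregnant when recruited, so the sampled women exposed later are those with longer pregnancies. A 36-week blood sample requires a pregnancy that reaches 36 weeks, yet Model 2 places maternal blood upstream of preterm birth.

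**Working it through.** The article states no sample size or count for these analyses, so there is no figure to reproduce. The check is date arithmetic.

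**Inputs.** Flood date 10 January 2011; first possible recruitment 4 April 2011; blood at 36 weeks; placenta and cord at birth (all from the article). Birth at 40 to 42 weeks as the upper end, and preterm as under 37 weeks, are assumptions; the article gives neither.

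**Lag.** 10 January to 4 April = 84 days; 84 / 7 = 12.0 weeks.

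**Latest gestation at flood that can yield a sample** = gestation at sampling − lag.

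| Recruited | Lag (weeks) | 36-week blood | Birth sample, birth at 40 weeks | Birth sample, birth at 42 weeks |
|---|---|---|---|---|
| 4 April | 12 | 36 − 12 = 24 | 40 − 12 = 28 | 42 − 12 = 30 |
| 4 weeks later | 16 | 20 | 24 | 26 |
| 8 weeks later | 20 | 16 | 20 | 22 |

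On a 0 to 40 week exposure window, at most 24/40 = 60 % is observable for blood and 28/40 = 70 % for placenta and cord (birth at 40 weeks).

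**Late recruits.** About 50 of 108 + 122 = 230 women (22 %) joined more than 10 months after the flood (Subjective, enduring distress from the flood). From 10 January to 10 November is 304 days, or 43.4 weeks, so all had delivered and none could give blood or birth samples.

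**Truncation of gestation length.** Earliest gestation at birth that can be sampled = gestation at flood + lag. With the 12-week lag:

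- 10 weeks at flood: birth at 22 weeks or later
- 20 weeks: 32 or later
- 24 weeks: 36 or later
- 25 weeks: 37 or later, so no preterm birth can be sampled

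The floor rises with exposure timing throughout the observable range.

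**Model 2.** A birth before 36 weeks has no 36-week blood, whatever the exposure timing. A birth at 36 weeks 0 days to 36 weeks 6 days may have it. The loss is therefore most preterm births, but not all.

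**The case against.** Several points on the other side stand.

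- A reader might infer that the article promises biomarker timing effects across the whole pregnancy. It does not. The analysis section names timing as a moderator, and the Discussion speaks of different points in pregnancy. Both are true of exposure up to about 28 weeks, where moderation remains estimable.
- A reader might infer that the model would fill in late exposure from its assumptions. No missing-data method is named for these models, so that cannot be charged to the plan.
- A reader might infer that Model 2 loses preterm birth altogether. Only the maternal-blood link is affected. Placenta and cord blood can come from preterm births in women exposed early enough and enrolled before delivery. Low birth weight, growth restriction and preeclampsia are not excluded in the same way.
- A reader might infer that a false timing effect is likely. Left truncation makes the direction certain: women already far on at the flood cannot have delivered earlier. The size depends on inputs outside the article. As an illustration with no true effect, take 7 % early births spread evenly from 22, 24 or 28 weeks to 37 weeks, and the rest normal with mean 39.6 and SD 1.2 weeks. Preterm birth is then 3.1 to 4.3 % for exposure at 27 weeks or later, against 8.0 to 8.4 % for the second trimester, with mean gestation 0.4 to 0.6 weeks longer. Other early-birth shapes give about 0.3 weeks. This is a main effect of timing in all eligible women; it does not demonstrate a spurious stress-by-timing interaction.
- Time since flood is fixed by gestation at flood when blood is drawn at one gestation. That is inherent in any single-date event and is not a planning error.
- Table 1 also marks the maternal-blood row under the flood assessment at recruitment. Blood drawn then would weaken the preterm point, but the row label and the section text both fix the draw at 36 weeks.

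One might also say that the analysable range is detail for a fuller analysis plan. That does not answer the point: the stated sampling rules leave part of a stated analysis without data and select one stated path on its outcome.

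**Conclusion.** The point holds in a limited form. For women recruited on the first day, 36-week blood covers exposure to about 24 weeks, and placenta and cord cover exposure to about 28 to 30 weeks. For everyone recruited later the limits are lower. The planned timing moderation has no data beyond them. Within the range, exposure timing and gestation length are linked by selection among women with birth samples. The maternal-blood link of Model 2 to preterm birth is tested after most preterm births have been removed.

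The limits rest only on the article's dates and sampling rules, plus the assumption that births occur by 40 to 42 weeks. How many women fall in each exposure band is not stated, so the effect on the actual sample cannot be sized. Questionnaire and child outcomes do not share the sampling gap, because women could join after delivery.

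**What to change.** 1. **Birth biologicals:** restrict the timing-moderation test and its conclusions to the exposure range actually observed for each sample type, and report sample counts by gestation at flood. Do not write in fixed cut-offs of 24 and 28 weeks: they hold only for first-day recruits, and a range restriction alone leaves the truncation in place.
2. **Discussion:** say that late-pregnancy exposure is not covered for these biomarkers.
3. **Model 2:** do not use preterm birth as an outcome of the 36-week maternal-blood path. Keep it for the placenta and cord-blood links, and keep the other complications.
4. **Gestation length and preterm birth:** analyse them against flood stress with a left-truncated (delayed-entry) time-to-birth model. When all women are analysed, entry is gestation on 10 January. For women enrolled while pregnant and for the birth-sample subset, entry is gestation at recruitment.

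The cost is narrower timing claims and slightly more analysis work. No new data are needed.

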Effects of PNMS from the ice storm have been found in nearly every domain of child development examined. Significant effects of the degree of maternal objective exposure to the disaster (but not maternal subjective distress) have been found on the children’s cognitive development [47-49], obesity [50], insulin secretion [51], brain development [52], and epigenetic signatures [53]. Effects of maternal subjective distress (and to a lesser extent, objective exposure) have been found on fingerprint asymmetry [54], autistic-like traits [55], and diagnoses of asthma [56] throughout childhood. Objective exposure and subjective distress from the ice storm have been found to interact such that the worst child outcomes are associated with mothers who presented a mismatch between objective exposure and subjective distress, that is, children of mothers with high objective stress but low subjective distress, or with low objective stress along with high distress [55]. There have also been significant timing effects: early pregnancy exposure seems to represent a window of vulnerability for cognition at age 2 years [47], and autism-like traits at age 6½ years [57], while second trimester exposure was associated with shorter gestation lengths and other birth outcomes [58], while worse motor outcomes have been associated with exposure in late pregnancy [59]. The sex of the child has often been found to moderate effects of PNMS: girls were found to be more vulnerable to effects of PNMS on asthma-related symptoms and diagnoses [56] and motor functioning [59], while boys seem to be more vulnerable for effects on fetal growth [58].

Although the Project Ice Storm sample is relatively small (n < 200), statistical power is enhanced by having a range of exposure levels from mild to severe; by the fact that the degree of exposure to the disaster was independent of family psychosocial attributes; by the acute onset of the event which allows exact dating of the stressor in the pregnancy; and by having detailed information on the women, their exposures, and their distress gathered relatively soon after the disaster. The independent nature of the disaster reduces the need to identify and control for all potential confounders, and allows one to disentangle the effects of the women’s objective exposure to the event from their cognitive appraisal of it, and from their subjective distress and hormonal responses.

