As such, this study included 2 main groups of participants:QF2011 women enrolled in M@NGO (n = 108, including 1 intrauterine death). These participants were enrolled in both M@NGO and QF2011. Some were already M@NGO study participants at the time of the floods and where subsequently recruited to QF2011; others were pregnant at the time of the floods and were recruited into both studies simultaneously. At recruitment to the QF2011 study, M@NGO women may still have been pregnant or they may have already given birth as the inclusion criteria stated only that they must have been pregnant on January 10, 2011.QF2011 women not enrolled in M@NGO (n = 122). This group included women who had declined participation, did not meet the selection criteria for the M@NGO study, or who were recruited after the close of M@NGO (May 31, 2011).

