##### Power

Our best estimates of effect sizes, and feasibility, come from Project Ice Storm which began with approximately 160 live births in 1998. Sixteen years later, there are still 75 families taking part in assessments. With this cohort, we have had sufficient statistical power to show significant effects of the severity and/or timing of ice storm stress on: gestational age, obstetric complications, IQ, language, memory, attention, internalizing and externalizing problems, autistic-like symptoms, fingerprint asymmetry, obesity, brain structure, and other outcomes. Although Project Ice Storm lacks the sample size to test important interactions and advanced modelling, these data nonetheless suggest that we have adequate statistical power with respect to the QF2011 study.

The QF2011 study noted an initial formal withdrawal rate of 15.9 % between recruitment and the first face-to-face assessments of infants at 16 months of age, the withdrawal rate at the 2½ year assessment dropped to 3.7 %. Moreover, of the 191 families remaining in the study at 16 months, 91.6 % completed some portion of the assessment. At age 2½ years, 175 families provided data. Currently, a sample of 209 families can be contacted for the 4 year assessment which began in 2015. Using a conservative participation rate of 80 %, it is estimated that data will be available for approximately 167 families at this assessment.

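### Gestational age at the flood is a lower bound on gestation length, so comparing late with earlier exposure on gestation length or preterm birth makes late exposure look protective

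*Protocol article*

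**What the plan says.** - **Eligibility** (Participants). QF2011 women "had to have been pregnant with a singleton pregnancy (at any gestation") on 10 January 2011. The same section confirms that some had already given birth when recruited, because "the inclusion criteria stated only that they must have been pregnant on January 10, 2011".
- **Recruitment** (Participants). "Recruitment for QF2011 began as soon as ethics approval was received (April 4, 2011), and continued to mid-January 2012".
- **Outcomes** (Problem statement, objectives, hypotheses and research questions). Model 2 leads to "obstetric complications (such as preterm birth, low birth weight, intrauterine growth restriction and preeclampsia"). The midwifery-care hypothesis in the same section names gestation length as a perinatal outcome.
- **Analysis** (Birth biologicals). Bivariate associations across the model come first, then structural equation modelling, "including testing of moderation of effects by fetal sex and by timing in gestation of the floods".
- **Replication aim.** The Problem statement sets out to replicate and extend Project Ice Storm. The section on that cohort reports that "second trimester exposure was associated with shorter gestation lengths and other birth outcomes". The Power section credits it with "significant effects of the severity and/or timing of ice storm stress on: gestational age, obstetric complications".

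The methods named are correlations, linear regression, multilevel models and structural equation models. None of them limits a comparison to women still pregnant at a given gestation.

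**The concern.** A woman at 36 weeks on the flood date cannot have delivered at 34 weeks, whereas a woman at 10 weeks still could. The timing variable therefore decides which values of the outcome can be observed. If mean gestation or the preterm rate is compared across flood timing as though every woman had been at risk since conception, women exposed late have longer gestation and fewer preterm births by construction.

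At stake is the reading of one of the study's leading questions, the gestational timing of the stressor. A difference between third-trimester and earlier exposure could be reported as a window of vulnerability when it only reflects who could enter the cohort.

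**Working it through.** The article gives no power, alpha or effect size for a timing test on these outcomes, so there is no figure of its own to reproduce.

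**Inputs from the article.** Inclusion requires G > g, where G is gestation length and g is gestational age on 10 January 2011. The sample is 108 + 122 = 230 women (Participants). Recruitment opened on 4 April 2011: 21 + 28 + 31 + 4 = 84 days, or 12 weeks, after the flood.

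**Assumptions, not in the article.** Two-sided 5% test. G is a mixture of N(39.6, 1.2) and a preterm tail N(34.5, 3) weeks, set to 5, 8 or 10% preterm. g is uniform from 4 to 42 weeks, kept if G > g. Timing has no effect on G.

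**Step 1: the bound.** With F the distribution function of G and S = 1 − F:

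E[G | G > g] = g + ∫ S(u) du / S(g), integrated from g upwards, and P(G < 37 | G > g) = [F(37) − F(g)] / S(g) for g < 37, and 0 from 37 weeks.

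The conditional mean cannot fall as g rises, and the preterm probability cannot rise. At 8% preterm:

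| Flood at (weeks) | Mean gestation (weeks) | Preterm |
|---|---|---|
| 8 or 20 | 39.17 | 8.0% |
| 32 | 39.32 | 6.4% |
| 36 | 39.55 | 2.3% |
| 37 | 39.62 | 0% |
| 39 | 40.20 | 0% |

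The table is flat from 8 to 20 weeks; the distortion comes mainly from exposure after about 32 weeks.

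**Step 2: false positives at n = 230 (2,000 cohorts per setting).**

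- Regression of G on g, at 8% preterm (range over 5 to 10%): spurious slope +0.16 week per 10 weeks later (0.12 to 0.19), rejection 26% (19 to 29%), virtually always favouring late exposure.
- Third versus first trimester: spurious +0.35 week (0.24 to 0.42), rejection 18% (13 to 20%).
- Preterm rate at the 8% setting: 7.9% if exposed before 28 weeks, 4.3% if later.

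A second set of runs, with g uniform on 2 to 42 weeks, a main component of N(39.5, 1.15) and 5.4 to 11.4% preterm, gave 17 to 22% rejection for the regression. Together the two sets span roughly 17 to 29%.

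**Step 3: dependence on late-exposed women.** Halving the share exposed at 28 weeks or later cut rejection from 23–27% to 13–15%; quartering it gave about 8%.

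**Step 4: the interaction.** With no stress effect, the stress-by-timing term rejected in about 3 to 5%. With stress raising preterm odds equally at all timings (assumed OR 1.8 per SD), a spurious interaction of +0.06 week per SD of each variable appeared, with rejection of 6.7% at n = 230 and 14% at n = 1,000.

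**Step 5: women enrolled while pregnant.** Here the bound is gestational age at recruitment, at least g + 12 weeks. The spurious slope was about +0.42 week per 10 weeks, with 27% (n = 100) to 42% (n = 150) rejection; both sizes are assumed.

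**Step 6: corrected analyses in the full cohort.** A Cox test with delayed entry at g rejected in 4.6 to 5.4%. Restriction to g < 24 weeks gave slopes of −0.004 to +0.004 week per 10 weeks and 4.9 to 5.6% rejection.

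**The case against.** The strongest objection is that the Birth biologicals sentence concerns moderation, a stress-by-timing interaction, and step 4 shows that test is barely touched. No regression of gestation length on timing is written out, and Data analysis and power describes its methods as only a sample. This stands in part. A reader might infer that the planned moderation test is itself invalid; the documents and the arithmetic do not support that. The main effect and trimester contrasts are still within reach of the plan, because timing is a stated research question, gestation length and preterm birth are stated outcomes, and a cohort with timing findings on gestation is to be replicated.

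A second objection is that late-exposed women are nearly absent from the birth-sample analyses. A woman at 30 weeks at the flood would have been at 30 + 12 = 42 weeks when recruitment opened. With exposure limited to 30 weeks or less, flood-date truncation alone gave 4.8 to 4.9% rejection. That is correct, but truncation at recruitment takes its place there (step 5), so entry at the flood date would be the wrong correction for that subset.

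A third is that the artefact cannot reproduce the predecessor's result. A reader might infer that it could pass as a replication of the second-trimester finding. It cannot by itself: step 1 gives equal means at 8 and 20 weeks, and first- versus second-trimester contrasts rejected in 4.5 to 5.9%. It can only create a difference from third-trimester exposure.

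Finally, a condensed article need not specify its survival models. The point is not a missing detail: the stated eligibility rule, timing variable and outcomes together produce the bias under the kinds of method named.

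**Conclusion.** The concern holds for timing main effects and for late- versus earlier-exposure contrasts on gestation length and preterm birth. The direction follows from the eligibility rule alone. The size rests on assumed distributions of gestation length and exposure timing: roughly 17 to 29% false positives at n = 230 against a nominal 5%, and fewer if late-exposed women are under-represented, which the article does not let one judge. Contrasts within the first two trimesters of the full cohort are essentially sound. The stress-by-timing interaction needs only a caveat, because it is distorted only if stress truly affects gestation, and then slightly at this sample size. The analysis should be changed for these two outcomes; the rest of the timing programme is not called into question by this point.

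**What to change.** For gestation length and preterm birth, test timing and severity-by-timing in a time-to-birth model on the gestational-age scale with delayed entry:

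- women enrolled while pregnant enter at their gestational age at QF2011 recruitment; this covers everyone in the birth-sample analyses;
- women enrolled after birth enter at their gestational age on 10 January 2011.

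A simpler alternative for the full cohort is to limit timing contrasts to exposure before about 24 weeks. This deals with the flood-date bound only. It does not remove the recruitment bound among women enrolled while pregnant, so it does not replace delayed entry in the birth-sample analyses.

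State that crude differences from third-trimester exposure in mean gestation or preterm rate will not be read as timing effects. The structural equation moderation test may stay, with this caveat for the two outcomes.

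The cost is analysis wording: gestational age at birth is already extracted from hospital records, and the flood date is fixed. The small downside is that hazard ratios are less directly comparable with the predecessor's differences in weeks.
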